**Fig. 2 Fig2:**
[figure not shown]
Schedule of enrolment, interventions and assessments

Participants allocated to the iCBT group will receive access to the *MUMentum* program via their Virtual Clinic account. All three lessons are required to be completed within the active treatment period, with one lesson released every seven days. The treatment period for study 1 is four weeks, which allows participants up to one week to complete each lesson and an additional week for revision. For study 2, the treatment period is six weeks, to allow participants up to two weeks to complete each lesson (without a revision week). Time to complete lessons was increased for study 2 as it was predicted this would be more suitable for postnatal women who are time-poor and adjusting to and caring for a newborn. There will be a five-day lockout period between lessons to ensure participants spend time revising and implementing the lesson material before moving onto the next lesson. At the beginning of each lesson, participants will complete the Kessler-10 psychological distress scale (K10) [33] as a brief measure of psychological distress, as well as two brief questions relating to time spent completing the previous lesson and homework activities. Participants will be notified of new lessons and reminded to stay on schedule via email and SMS reminders. One week after the active treatment period ends, participants will receive post-treatment questionnaires, with follow-up questionnaires completed four weeks later.

Participants allocated to the TAU group will receive access to questionnaires at each primary data collection point (i.e. baseline, post treatment, follow-up) via their Virtual Clinic account. The total trial period is nine weeks for study 1 and 11 weeks for study 2. As this is a ‘treatment as usual’ controlled study, all participants in the control group will have access to their usual care (i.e. continuation of their current maternity care). Information will be collected from participants regarding usual care. For ethical reasons, participants in the TAU group will be offered access to both the *MUMentum Pregnancy* and *MUMentum Postnatal* iCBT programs at conclusion of the study period.

#### Safety protocol

The *MUMentum* programs are unguided (i.e. no clinician support regarding program content) interventions with risk monitoring. Computer-generated alert emails will be sent to participants at completion of questionnaires if there is an increase in psychological distress as measured on the K10 before each lesson (i.e. one standard deviation increase from previous score and/or total score ≥ 30), depression as measured on the PHQ-9 at primary data collection points (i.e. one standard deviation increase from previous score and/or total score ≥ 23) or suicidality scores as measured on item 9 of PHQ-9, item 10 of EPDS, and item 9 on BDI-II at primary data collection points (i.e. score > 1). Alert emails will notify participants of increases in scores, where to seek additional support (e.g. GP) and emergency contact numbers. For both studies, alert emails will be monitored by the study clinician (i.e. psychiatry registrar; clinical psychologist) and contact will be made with the participant only if additional action to the automated alert email is required (e.g. phone call). Each participant’s GP will be notified via letter that their patient is enrolled in our research study and will be contacted further if safety concerns for their patient arise during the trial or their patient is withdrawn.

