**Methods/Design:**

Women who are pregnant (study 1) or < 12 months postpartum (study 2) with current clinically elevated symptoms of anxiety and/or depression according to validated self-report measures, will be recruited via the research arm of a not-for-profit clinical and research unit in Australia and randomised to the intervention group or treatment as usual control group. The minimum sample size for each study (alpha 0.05; power 0.80 for a *g* of 0.80) was identified as 50 with at least 10% more to be recruited to account for expected attrition. The co-primary outcome measures are the Patient Health Questionnaire 9-item scale and Generalised Anxiety Disorder 7-item scale to measure depression and anxiety symptom severity, respectively, and will be administered at the following primary time-points: baseline; post treatment; and at one-month follow-up. Psychological distress will be measured according to the Kessler-10 psychological distress scale at each primary time-point and will also be completed before each lesson for those in the intervention group. The total trial period nine weeks for study 1 and 11 weeks for study 2. Program efficacy will be determined using intent-to-treat mixed models. Maintenance of gains will be assessed at one-month follow-up.

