#### Inclusion criteria

Both studies will recruit adult women aged > 18 years, who are 13–30 weeks pregnant (study 1) or within 12 months postpartum (study 2). Applicants will meet clinical cut-off scores (>9) for anxiety and/or depressive symptoms as measured on the Generalised Anxiety Disorder 7-item version (GAD-7) [30] and Patient Health Questionnaire 9-item version (PHQ-9) [31]. Additional inclusion criteria are as follows: computer and Internet access; Australian resident; fluent in written and spoken English; willing to provide name, phone number and address, and to provide the name and address of their GP.

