#### Randomisation and allocation procedures

Online applications meeting the study’s inclusion criteria will be randomised to either iCBT or a TAU control group according to a 1:1 ratio within blocks of 20. Because the two trials were conducted using different software, the randomisation procedure differs slightly between the studies.

For study 1, the allocation sequence will be generated by an independent person not involved in the study, using a random number generator (https://www.random.org/). The numbers corresponding to the treatment group (1 = iCBT) or the control group (2 = TAU) will be placed in sequentially numbered, sealed opaque envelopes. The randomisation envelopes will then be assigned manually (by the study coordinator) to the successful online application in order of application date. Once matched, the group allocation will be revealed and participants will be notified of their group allocation by e-mail.

For study 2, which will be conducted in an updated Virtual Clinic web system,^1^ the randomisation sequence will be electronically uploaded to the server by an independent person not involved in the study. Successful applicants will be notified via e-mail of their acceptance into the study and automatically randomised to treatment group (1 = CBT) or control group (2 = TAU).

Once randomised, participants and research personnel will not be blinded to group condition. Participants in the intervention group and control group will login to https://virtualclinic.org.au/ and complete baseline (pre-treatment) questionnaires. The three primary data collection points for study participants in iCBT group and TAU group are as follows: baseline (pre-treatment), post treatment, and at one-month follow-up (see Fig. 2). Participants will receive notifications and reminders to complete questionnaires via computer-generated emails, SMS and follow-up phone calls from the research team. We will track reasons for non-adherence (e.g. lost to follow-up). As this is an unguided program, participant enquiries (e.g. technical issues) will be responded to by research technicians; no coaching or support with program content will be provided.

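### The K10 distress alert covers only pre-lesson scores, so K10 scores collected at post treatment and one-month follow-up send no K10 alert in either arm

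*Protocol article*

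**What the plan says.** The Safety protocol section gives each alert its own timing.

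- **K10:** an alert follows "an increase in psychological distress as measured on the K10 before each lesson". The trigger is a rise of one standard deviation from the previous score, a total of 30 or more, or both.
- **PHQ-9:** an alert follows a rise in "depression as measured on the PHQ-9 at primary data collection points". The trigger is a rise of one standard deviation, a total of 23 or more, or both.
- **Suicidality items** (PHQ-9 item 9, EPDS item 10, BDI-II item 9): an alert follows a score above 1, also at the primary points.

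On delivery: "Computer-generated alert emails will be sent to participants at completion of questionnaires". The study clinician monitors the alert emails and contacts the woman if more is needed. Her GP is contacted if safety concerns arise.

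The K10 schedule is wider than the K10 alert. The abstract states: "Psychological distress will be measured according to the Kessler-10 psychological distress scale at each primary time-point", with further K10 scores before each lesson in the intervention group. For the comparator, the text after Fig. 2 in the Procedures says: "Participants allocated to the TAU group will receive access to questionnaires at each primary data collection point". TAU women are offered the programs only once the study period is over.

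**The concern.** The trial describes its programs as unguided but with risk monitoring. A K10 total that prompts a support email and a clinician's attention before Lesson 3 prompts neither at post treatment or follow-up, unless a depression or suicidality trigger is also met.

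The alerts that do run at those points concern depression and suicidality. None concerns anxiety or general distress: the section gives no GAD-7 trigger, and the K10 trigger does not apply there. Yet anxiety is a co-primary outcome and is enough on its own for entry: "Applicants will meet clinical cut-off scores (>9) for anxiety and/or depressive symptoms". The protocol's own description of the K10, under Secondary outcomes, presents it as useful for monitoring iCBT patients and as able to identify depression and some anxiety disorders in pregnant women. The measure best placed to fill the gap is collected at these points and not used for alerts.

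What is at stake is participant safety at the margin, not the validity of the comparison.

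**Working it through.** The plan states no figure to reproduce. The check counts K10 occasions per woman and matches each to the alert rules.

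**Inputs**
- Primary points: 3 per arm (baseline, post treatment, one-month follow-up), from the Randomisation and allocation procedures section.
- Lessons: 3, iCBT arm only, each opened by a K10, from the text after Fig. 2.
- K10 at each primary point in addition to pre-lesson scores, from the abstract.
- Alert rules, from the Safety protocol section.
- Minimum sample per study: 50 plus at least 10% for attrition, from the Statistical Methods section.

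**Occasions and coverage**

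| | iCBT | TAU |
|---|---|---|
| All K10 occasions | 3 primary + 3 pre-lesson = 6 | 3 primary |
| K10 occasions after baseline | 6 − 1 = 5 | 3 − 1 = 2 |
| Of these, with a K10 alert as written | 3 of 5 | 0 of 2 |
| With follow-up added | 4 of 5 | 1 of 2 |
| With post treatment and follow-up added | 5 of 5 | 2 of 2 |

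At post treatment and follow-up taken alone, K10 alert coverage is 0 of 2 in each arm. The active alerts at those two points are identical across arms: PHQ-9 and three suicidality items.

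**A worked case**
- K10 of 32 before Lesson 3: at or above 30, so an alert is sent and the clinician sees it.
- K10 of 32 at post treatment, PHQ-9 of 18 without a rise of one standard deviation, suicidality items at 0 or 1: 18 is below 23 and no item exceeds 1, so no alert is sent. Clinician monitoring is attached to alert emails, so that route gives the clinician no prompt either.

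**Volume of extra alerts**
- Minimum n per study: 50 × 1.10 = 55.
- Both points added: at most 2 × 55 = 110 alerts per study.
- Follow-up only: at most 1 × 55 = 55 alerts per study.
- These ceilings rise in proportion if more than 55 are recruited. For example, 75 women would give at most 2 × 75 = 150.

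**Order of alert and outcome**
Alerts go out once questionnaires are complete. A post-treatment alert therefore cannot alter the post-treatment scores, but it precedes the follow-up scores collected four weeks later. A follow-up alert comes after the last assessment and can alter no outcome.

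**The case against.** The strongest reply is that the split is coherent and probably deliberate. Between primary points the K10 is the only symptom scale described, so it carries the alert there. At primary points a depression score and three suicidality items are available, and these more specific measures carry it instead. Both arms are treated alike at those points. Other cover exists too: GPs can be contacted about any safety concern, the research team can see identifiable data to follow progress, and TAU women keep their usual maternity care. Much of this stands. It limits the point to an optional improvement.

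It does not remove the point, because none of the triggers at post treatment or follow-up responds to anxiety or general distress. Nor is this detail that an article leaves to a fuller document: the section states when each trigger applies.

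The reply is also right about cost. The K10 threshold of 30 fires without any worsening, in women enrolled for elevated symptoms. If the program works, K10 scores at post treatment would be higher in TAU, so alerts urging women to seek support would fire more often there. That is a differential prompt before the one-month assessment.

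A reader might infer three stronger things.
- **That the protocol contradicts itself.** It does not. Collecting the K10 at a time-point does not oblige the plan to attach an alert to it.
- **That women are unmonitored at post treatment and follow-up, or that TAU women are less protected there.** PHQ-9 and suicidality alerts run at those points in both arms on the same terms.
- **That the gap biases the results.** Nothing in the analysis depends on the missing alert.

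**Conclusion.** The point holds as a low-severity gap in safety coverage. K10 scores already collected at post treatment and follow-up trigger no K10 alert in either arm, and TAU women have none during the trial. The remaining exposure is a woman whose distress or anxiety is high or rising while her PHQ-9 stays below 23 without a rise of one standard deviation and no suicidality item exceeds 1. The documents give no basis for estimating how many such women there will be.

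This rests on reading the K10 timing literally and on the K10 schedule stated in the abstract. Fig. 2 is not shown, but the abstract is explicit enough not to need it. It also assumes that alerts are sent after the full set of questionnaires at a time-point is complete. No estimate, test or conclusion of the trial changes because of the gap.

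**What to change.** In the Safety protocol section, extend the K10 trigger so that it applies to pre-lesson scores and also to post-treatment and follow-up scores, in both groups. Keep the same thresholds, automated email and study clinician monitoring. Baseline need not be added.

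Costs:
- No new measure or visit. At most 2 extra alerts per woman, or 110 per study at 55 women, some going to women whose K10 is high but stable.
- A protocol wording change and a settings change. The article notes, "Because the two trials were conducted using different software", that randomisation differs between the studies, so the setting would probably need changing in two places.
- The change comes mid-trial. The Trial status section reports 98 women randomised across both studies, against a combined minimum of 2 × 55 = 110, so earlier and later women would be handled differently.
- If the program works, the post-treatment alert would probably fire more often in TAU. It could prompt help-seeking that slightly reduces the one-month contrast, as the existing PHQ-9 alert already can.

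If that last cost is a concern, add the K10 alert at follow-up only. That closes half of the gap, with at most 55 extra alerts per study at 55 women, and cannot affect any outcome.

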#### Primary outcomes measures

All measures will be collected at specified time-points throughout the trial as outlined in Fig. 2. As this study is evaluating a transdiagnostic iCBT program, the co-primary outcomes will be anxiety and depression symptom severity.

*Patient Health Questionnaire 9-item scale* (PHQ-9) [31]. The PHQ-9 is a nine-item self-report measure of depressive symptoms experienced over the past two weeks. The PHQ-9 is based on the Diagnostic Statistical Manual, fourth edition (DSM-IV) [34] diagnostic criteria for major depressive disorder (MDD). Participants rate the frequency of symptoms (e.g. ‘Feeling down, depressed, or hopeless’) on a 4-point scale ranging from 0 (not at all) to 3 (nearly every day). Total scores range from 0 (no symptoms) to 27 (severe symptoms). Scores > 9 are indicative of a clinically significant level of depressive symptoms (i.e. diagnosis of depression). The measure demonstrates sound psychometric properties [31], has been used extensively to measure treatment outcomes during iCBT interventions targeting depression and anxiety [25], and has been validated in pregnancy and postpartum samples [35, 36].

*Generalized Anxiety Disorder 7 item scale* (GAD-7) [30]. The GAD-7 is a seven-item self-report measure of general anxiety symptoms experienced over the past two weeks. The GAD-7 is based on DSM-IV criteria for generalised anxiety disorder (GAD). Items (e.g. ‘Feeling nervous, anxious, or on edge’) are rated on a 4-point scale ranging from 0 (not at all) to 3 (nearly every day). Total scores are in the range of 0–21, with scores > 9 indicating the possibility of an anxiety disorder. The GAD-7 has been validated for diagnosing GAD in the general population and demonstrates good internal consistency and test–retest reliability [30, 37]. The GAD-7 has been validated for identifying GAD in a sample of pregnant women, with a cut-off score of 13 demonstrating a sensitivity of 61% and specificity of 73% [38].

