## Objectives

The primary aim of the proposed studies is to test the acceptability and the efficacy of the iCBT *MUMentum* programs—*MUMentum Pregnancy* (study 1) and *MUMentum Postnatal* (study 2)—in reducing symptoms of anxiety, depression and overall psychological distress compared to usual care in the perinatal period. We hypothesise that the two iCBT interventions will significantly reduce symptoms of distress, anxiety and depression and will be significantly more effective than usual care. The secondary aim is to explore the effects of the iCBT programs on mother–infant bonding, parenting confidence and maternal quality of life. We hypothesise that the iCBT programs will lead to significant improvements in these three factors compared with usual care.

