#### Secondary outcomes

*Kessler-10 psychological distress scale* (K10) [33]*.* The K10 is a ten-item self-report measure designed to assess general (i.e. non-specific) psychological distress over the past 30 days. For the current RCTs, the time frame was modified to assess distress in the past two weeks. Items (e.g. ‘About how often did you feel hopeless?’) are rated on a 5-point scale ranging from 1 (none of the time) to 5 (all of the time). Total scores range from 10 (no distress) to 50 (severe distress). The K10 demonstrates strong psychometric properties in non-perinatal samples [39] and is advantageous for monitoring iCBT patients [40]. The K10 has also demonstrated acceptable sensitivity and specificity in identifying depression and some anxiety disorders in pregnant women [41].

*Edinburgh Postnatal Depression Scale* (EPDS) [42]. The EPDS is a ten-item self-report screening tool originally developed to detect symptoms of postpartum depression, although it is also used to assess for depression during pregnancy [43]. The EPDS enquires as to the intensity of symptoms over the past seven days (e.g. ‘I have felt sad or miserable’; ‘I have blamed myself unnecessarily when things went wrong’). Items are rated on a scale from 0 (e.g. no, not at all) to 3 (e.g. yes, most of the time), with a maximum total score of 30. A total score of > 12 is indicative of possible depression. The EPDS is well validated as a screening tool in antenatal and postpartum samples, with sensitivity in the range of 70–85% and specificity in the range of 77–85% in identifying a major depressive episode [20, 44, 45].

*World Health Organization Quality of Life* (WHOQOL-BREF) [46]. The WHOQOL-BREF is a 26-item self-report measure assessing quality of life (QOL) over the past four weeks. QOL is measured across four domains: physical health (e.g. sleep, pain); psychological health (e.g. self-esteem, concentration); social relationships (e.g. support; personal relationships); and environment (e.g. physical safety; financial resources). Items (e.g. ‘How much do you enjoy life?’) are rated on a 5-point Likert scale ranging from 1 (e.g. not at all) to 5 (e.g. an extreme amount). The WHOQOL-BREF has been validated in postpartum women, with satisfactory internal consistency and high discriminant validity [47]. The computerised version of the WHOQOL-BREF has demonstrated excellent psychometric properties [48].

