### Statistical Methods

As there is limited research outlining the efficacy of iCBT for the treatment of perinatal anxiety and depression, power calculation of sample size (using ClinTools software) was informed by a published RCT of a transdiagnostic iCBT program [25]. To detect a between-group effect corresponding to Hedges’ *g* of 0.80, the minimum sample size for each group (alpha set at 0.05, power at 0.80) was identified as 25 per group. At least 10% more will be recruited to account for expected attrition.

All analyses will be conducted at conclusion of the trial when the desired sample size has been obtained. All analyses will be conducted using Statistical Package for the Social Sciences (IBM SPSS, IBM Corp., Armonk, NY, USA). Significance testing of group differences regarding demographic data and pre-treatment measurements will be conducted using analysis of variance (ANOVA) and Chi square (χ2) where the variables consist of nominal (or categorical) data.

Intent-to-treat (ITT) mixed models using restricted maximum likelihood (REML) estimation will be used to account for missing data due to participant dropout. Mixed models do not assume that the last measurement is stable (the last observation carried forward assumption) [58]. REML models are appropriate for RCTs with multiple time-points and pre- to post-only designs [59]. The assumption that data are missing at random will be evaluated using binary logistic regression to predict dropout and by comparing these two groups (those with missing data to those with complete data) on baseline measures. Significant effects will be followed up with pairwise contrasts comparing mean post-treatment (and follow-up) scores between groups. Effect sizes will be calculated between groups (Hedges’ *g* to account for small sample size) and within groups (Cohen’s *d*, adjusting for the repeated measures correlation) using the pooled standard deviation and adjusted for sample size. Post-hoc exploratory mediation analyses, using the PROCESS syntax for SPSS PROCESS [60], will be used to examine the associations between symptom change and changes in the maternal factors of mother–infant bonding, parenting confidence and maternal quality of life.

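### Two co-primary scales, a sample size for one comparison, and no success rule or single primary time-point: either the 5% error rate or the 80% power is not met

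*Protocol article*

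**What the plan says.** The Primary outcomes measures section of the protocol article states that "the co-primary outcomes will be anxiety and depression symptom severity" and then describes PHQ-9 and GAD-7. In the Abstract (Methods/Design), these scales "will be administered at the following primary time-points: baseline; post treatment; and at one-month follow-up". The same paragraph gives the one-month visit the role of assessing whether gains are maintained.

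Under Statistical Methods, "the minimum sample size for each group (alpha set at 0.05, power at 0.80) was identified as 25 per group", for a Hedges' g of 0.80. The Abstract repeats this as 50 per study, with at least 10% added for attrition. These sample-size statements are the only place where an alpha appears. The analysis is a mixed model, after which "Significant effects will be followed up with pairwise contrasts comparing mean post-treatment (and follow-up) scores between groups".

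The Objectives section sets the hypothesis: "We hypothesise that the two iCBT interventions will significantly reduce symptoms of distress, anxiety and depression and will be significantly more effective than usual care". Distress is measured by K10, which is described under Secondary outcomes: "The K10 is a ten-item self-report measure designed to assess general (i.e. non-specific) psychological distress".

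No section says whether one or both co-primary scales must be significant, or at which visit the efficacy claim is decided.

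**The concern.** With two co-primary outcomes, the type I error and the power of the efficacy claim both depend on the success rule. If either scale can carry the claim, there are two chances of a false positive. If both must succeed, there are two chances of a miss. A calculation for one comparison matches neither rule.

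Without a rule, the choice could be made after the results are seen. A trial significant on GAD-7 but not on PHQ-9 could be reported as positive or as negative, and the article would not contradict either report. Such a split result is foreseeable, because eligibility is by elevated anxiety and/or depressive symptoms, so some women will enter with little room to improve on one scale.

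Two related gaps add to this. Both post-baseline visits carry the label primary, so the visit that decides efficacy is open. The Objectives and the outcome list also disagree on whether distress belongs to the primary claim.

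**Working it through.** **Inputs from the protocol article.** g = 0.80, alpha 0.05, power 0.80 and 25 per group (Statistical Methods); 1:1 allocation (Randomisation and allocation procedures); two co-primary scales (Primary outcomes measures).

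**Inputs assumed.** Tests are two-sided, which is not stated but is the version that reproduces the plan's number. The correlation between the PHQ-9 and GAD-7 test statistics is 0.3 to 0.8. The article gives no value and says only that the two conditions are often highly co-morbid. Where correlation between visits matters, it is taken as 0.5 to 0.7.

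**1. The plan's own figure.** n per group = 2 × [(1.960 + 0.842)/0.80]² = 24.53, rounded up to 25. This reproduces the stated number for a single two-sided comparison; a one-sided test would need 20. By the exact t-test, 25 per group gives power 0.791. The stated size is therefore right for one scale at one visit.

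**2. Either scale suffices, each at 0.05.** With independent scales the error is 1 − 0.95² = 9.75%. Simulating correlated normal statistics gives:

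| Correlation between scales | Familywise error |
|---|---|
| 0.3 | 9.5% |
| 0.5 | 9.1% |
| 0.7 | 8.3% |
| 0.8 | 7.8% |

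**3. Both scales required, each at 0.05.** The error is at most 5%, because a false claim needs a false rejection on at least one scale whose null is true. Power at 25 per group with g = 0.80 on both scales is bounded by the single-scale values. By the exact t-test it lies between 0.791² = 0.63 (independent) and 0.79 (perfectly correlated). Simulated t-tests give about 0.65 at correlation 0.3, 0.67 at 0.5, 0.70 at 0.7 and 0.72 at 0.8. The normal approximation is slightly higher: 0.68 at 0.3 and 0.74 at 0.8. All are below 0.80.

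**4. The two visits.** Statistical Methods runs the visit contrasts only after a significant effect. If that effect is the joint two-degree-of-freedom test of group difference at the two visits, then:

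- the chance of a significant model effect and at least one significant contrast is 3.7 to 4.2% within one scale;
- across both scales it is 6.1 to 8.0%;
- the chance of a significant model effect on either scale is 7.9 to 9.6%.

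The excess over 5% comes from the two scales, not from the two visits. The article does not name the gating effect, so this protection is itself an assumption.

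**5. Power under a Holm rule at 25 per group.** The smaller p-value is tested at 0.025. If it is significant, the other is tested at 0.05. With g = 0.80 on both scales, power per scale is about 0.75. With benefit on one scale only, it is close to the Bonferroni value at 0.025, which is 0.70 by the exact t-test. The unadjusted figure is 0.79. To keep 0.80 at 0.025, n = 30 per group (31 by the exact t-test).

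**The case against.** The strongest reply is that nothing in the article licenses a claim on either scale alone. The hypothesis joins the outcomes with the word and, and co-primary often means that both must succeed. On that reading the error is controlled without adjustment. This is fair, and it is why the inflated error can only be stated conditionally. It does not close the matter. Power then falls below the stated 0.80. The same sentence also includes distress, so taken literally it would require K10 as well, which conflicts with K10's place among the secondary outcomes.

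A reader might infer that every scale, both visits and K10 are all tested at 0.05, so that the error is far above 5%. The documents do not support this. Alpha 0.05 is written only in the sample-size statements. The visit contrasts are gated by a significant effect, the list of primary time-points includes baseline and so reads as a data-collection label, and follow-up is given a maintenance role. K10 is labelled secondary. The two visits and K10 should not be counted as further free chances.

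It can also be said that a journal article may leave multiplicity to the analysis plan. That holds for the adjustment method. It does not hold for naming two co-primaries while sizing for one comparison, since both are fixed in this document and do not fit each other.

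Finally, the mixed model uses the baseline scores and may recover some power. That depends on a correlation between visits that the article does not give, and the stated power does not rely on it.

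**Conclusion.** The point holds as a conditional one. The success rule for the two co-primary scales and the primary time-point are undefined, and the stated alpha and power cannot both hold for the efficacy claim at 25 per group. With an unadjusted either-scale rule, the familywise error is about 8 to 9.5%. With a both-scales rule, it is at most 5% and power is about 0.65 to 0.72 instead of 0.80. These figures assume two-sided tests, a correlation of 0.3 to 0.8 between the scales and, for power, g = 0.80 on both.

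The mismatch over distress between the Objectives and the outcome list is real but minor. It needs no calculation.

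The article does not commit the trial to an inflated error rate; it leaves open which property is lost. This should be fixed before analysis, but it does not undermine the design.

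**What to change.** In a dated amendment or in the analysis plan, before any outcome data are analysed:

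1. Name post-treatment as the single primary time-point and one-month follow-up as secondary, for maintenance of gains. The Abstract already describes follow-up this way.
2. State the success rule. Preferred: test PHQ-9 and GAD-7 by Holm at a two-sided familywise 0.05, with any claim limited to the scale on which it is shown. This fits the and/or eligibility. Requiring both scales at 0.05 is also valid and closer to the wording of the hypothesis; if that is intended, say so.
3. Restate the power at 25 per group under the chosen rule. For Holm it is about 0.75 per scale if both scales benefit and about 0.70 if only one does, against 0.79 unadjusted. For both required it is about 0.65 to 0.72.
4. Keep K10 secondary and take distress out of the primary hypothesis.
5. Name the model effect that must be significant before the visit contrasts are run.

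The cost is wording plus an openly stated loss of power, with no additional participants. If the sponsor wants 0.80 on a scale tested at 0.025, 30 to 31 analysed per group are needed instead of 25. The Trial status section says recruitment was ongoing, and Statistical Methods places all analyses at the end of the trial, so on the article's own account the change can precede the analysis.
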